### Interim analyses {21b}

There are no interim analyses planned.

### Methods for additional analyses (e.g. subgroup analyses) {20b}

For the three primary cluster-C PDs (avoidant, dependent, obsessive-compulsive) and the otherwise specified PD with predominantly cluster-C traits, subgroup analyses are planned.

### Methods in analysis to handle protocol non-adherence and any statistical methods to handle missing data {20c}

The primary outcome will be assessed using an analysis. Missing data will be reduced to a minimum by using the appropriate measures described above.

### Plans to give access to the full protocol, participant-level data and statistical code {31c}

The full protocol can be made available by the corresponding author upon reasonable request and in agreement with the research collaboration.

Because of the sensitivity of the data and the strict policies for data security, we will not share our participant-level data with external parties or in external repositories.

## Oversight and monitoring

### Composition of the coordinating Centre and trial steering committee {5d}

This is a mono-centre study designed, performed and coordinated in Arkin/NPI. Day to day support for the trial is provided by:Principal investigator: takes supervision of the trial and medical responsibility of the patients.Data manager: organizes data capture, safeguards quality and data.Study coordinator: trial registration, coordinates the study, annual safety reports.Research assistants: identify potential recruits, take informed consent, conduct interviews and ensure follow-up according to protocol.The research committee meets biweekly. There is no trial steering committee or stakeholder and public involvement group.

### Composition of the data monitoring committee, its role and reporting structure {21a}

In agreement with the ethical committee of the VU, a DSMB has not been appointed for this study.

### Adverse event reporting and harms {22}

There are no direct risks involved for patients enrolled in this study. All patients will receive an evidence-based treatment (i.e. SPSP, APT or ST). Adverse events are defined as any undesirable experience occurring to a subject during the study, whether or not considered related to the experimental intervention. All adverse events reported spontaneously by the subject or observed by the investigator or his staff will be recorded. Serious adverse events will be reported within 24 h to the principal investigator.

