### Criteria for discontinuing or modifying allocated interventions {11b}

Patients can leave the study at any moment for any reason if they wish to do so, with the possibility of finishing the treatment (research dropout). Also, the therapist or the investigator can decide to withdraw a subject from the study for urgent (medical) reasons. Discontinuing treatment is possible in case of a severe psychiatric disorder requiring priority in treatment, deterioration/worsening of the disorder and practical reasons of insufficient commitment/motivation (treatment dropout). It is not possible to switch between different treatments (SPSP, APT and ST) in the trial. If there is a need for further treatment, the patient is offered a regular treatment at the NPI or will be referred.

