### Provisions for post-trial care {30}

Patients who drop out from treatments will be referred for regular clinical care. During the follow-up period, no specific interventions are offered. Patients are referred to their general practitioner if clinically necessary. Patients can apply for additional treatment 6 months after treatment termination (18 months after start treatment) with a referral from their general practitioner. In case of additional treatment, patients will not return to the same therapist.

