#### Treatment retention

In case of dropout of treatment, the therapist completes a questionnaire that assesses the reasons for dropout. The research assistant invites the patient for an exit interview and motivates the patient for completing additional assessments that were scheduled at the beginning of treatment. Patients are considered early completers if both patient and therapist consider the treatment as being successful. Another possibility is a ‘push out’ of the treatment program for various reasons, e.g. if commitment problems persists, treatment has negative effects or if the safety of therapists is endangered in other ways.

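### Adverse events are captured passively under a no-direct-risk premise that sits badly with the protocol's own text; if retention differs, recorded counts by arm may partly reflect retention

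*Protocol article*

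**What the plan says.** The protocol article, under Adverse event reporting and harms {22}, begins with "There are no direct risks involved for patients enrolled in this study" and supports this by calling all three treatments evidence-based. The definition that follows is wide: "Adverse events are defined as any undesirable experience occurring to a subject during the study", related to treatment or not. The method of collection is then fixed: "All adverse events reported spontaneously by the subject or observed by the investigator or his staff will be recorded". Serious events go to the principal investigator within 24 hours. No checklist or scheduled question about events is stated.

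Two other sections bear on the premise. Criteria for discontinuing or modifying allocated interventions {11b} lists, among the grounds for stopping treatment, "deterioration/worsening of the disorder and practical reasons of insufficient commitment/motivation (treatment dropout". Treatment retention says a patient may be pushed out "if commitment problems persists, treatment has negative effects or if the safety of therapists is endangered in other ways".

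Treatment retention also sets out what happens when a patient leaves: "In case of dropout of treatment, the therapist completes a questionnaire that assesses the reasons for dropout", and "The research assistant invites the patient for an exit interview and motivates the patient for completing additional assessments that were scheduled". For the period after therapy, Provisions for post-trial care {30} says "During the follow-up period, no specific interventions are offered", with referral to the general practitioner where clinically needed.

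**The concern.** The definition of an event covers the whole study, and assessments run to 36 months. The stated capture routes depend on a patient volunteering something or on staff noticing it. Both are most likely while the patient sees a therapist once or twice a week. After therapy, the stated study contact is the scheduled assessments, at 12, 18, 24 and 36 months in the later phase, plus researchers contacting patients where responses are missing. Leavers have an additional, different route through the dropout questionnaire and exit interview. The chance that an event is recorded may therefore depend on whether and when a patient leaves therapy, and the article itself plans to test whether retention differs between treatments.

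Few other stated mechanisms would reveal uneven reporting. Therapists are not blinded, there is no data monitoring committee, and no audit is planned. An analysis plan cannot recover events that nobody asked about, so this is a matter of the stated collection method and not of analysis detail held elsewhere.

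At stake is how far event counts by arm can be read. In a head-to-head trial of three active therapies, readers will look at those counts whether or not a test is planned.

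**Working it through.** **No figure to reproduce.** The article gives no adverse event rate, no dropout rate and no harm calculation. The sample size of 88 per arm plays no part here.

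**The premise against the other sections.** Negative effects of treatment as a ground for push-out cannot stand beside a statement of no direct risks without explanation. Worsening of the disorder as a ground for stopping is a weaker tension, because a disorder can worsen without the treatment being the cause.

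**Length of therapy contact.** 32 sessions at two a week plus 18 weekly sessions take 32/2 + 18 = 34 weeks, about 7.8 months. Trial design {8} gives 4–5 plus 4–5 months, so 8–10. The stated maximum is 12. The part of 36 months after planned therapy is then:
- 8 months of therapy: 28/36 = 78%
- 10 months: 26/36 = 72%
- 12 months: 24/36 = 67%

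The planned dose is the same in every arm, so this share creates no difference between arms by itself. It shows only how much of the study lies outside regular sessions.

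**Illustration of the dependence on retention.** All inputs here are assumptions: equal true event rate r per month in two arms; a fraction D of patients leaves at month 3; an event is recorded with probability 0.8 during therapy and p afterwards; therapy lasts L months and observation T months. Expected recorded events per patient are

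r × {(1 − D)[0.8L + p(T − L)] + D[0.8 × 3 + p(T − 3)]}.

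For L = T = 12, D = 15% versus 40% and p = 0:
- lower-dropout arm: 0.85 × 9.6 + 0.15 × 2.4 = 8.52 (times r)
- higher-dropout arm: 0.60 × 9.6 + 0.40 × 2.4 = 6.72 (times r)
- ratio: 6.72/8.52 = 0.79

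Ratio of recorded events, higher-dropout arm to lower-dropout arm, L = T = 12:

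| Dropout | p = 0.8 | p = 0.4 | p = 0.2 | p = 0 |
|---|---|---|---|---|
| 10% v 20% | 1.00 | 0.96 | 0.94 | 0.92 |
| 10% v 30% | 1.00 | 0.92 | 0.88 | 0.84 |
| 15% v 40% | 1.00 | 0.90 | 0.85 | 0.79 |

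With L = 10 and T = 36 the same scenarios run from 1.00 to 0.80. The ratio is 1.00 whenever dropout is equal or detection is the same in and out of therapy.

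**Reversal.** Suppose the dropout questionnaire and exit interview yield q further recorded events per leaver. In the most extreme cell, with r assumed at 0.05 per month, the shortfall is 0.05 × (8.52 − 6.72) = 0.09 events per patient. The exit route adds (0.40 − 0.15)q = 0.25q to the higher-dropout arm relative to the other. The two balance at q = 0.09/0.25 = 0.36. Above that, the arm with more dropout shows more recorded events, although the true background rate is equal.

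**The case against.** A reader might infer that the harm comparison is biased in favour of the arm with more dropout. The document does not support that. It describes no between-arm harm analysis and gives no dropout rate by arm. It also provides contact outside therapy: the dropout questionnaire, the exit interview, the remaining scheduled assessments, and researchers who check responses during follow-up. Observations by these staff plausibly count under the stated rule. Patients who leave because of negative effects are the ones whose reasons are collected, so that arm could show more recorded harm. Testing differential retention is also not the same as expecting it.

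A reader might also infer that the trial could not tell whether one therapy produces more deterioration. That does not follow either. The ADP-IV is analysed by intention to treat with all available data on one assessment calendar, the BSI is a secondary outcome, and reliable change is among the planned secondary outcomes.

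Finally, the no-risk sentence can be read as saying that enrolment adds no risk, since all three therapies are regular care at the site. That reading eases the tension with worsening of the disorder. It does not remove the conflict with negative effects of treatment.

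What stands against these points is narrow. The exit routes are triggered only by dropout and, as described, the questionnaire asks for reasons for leaving and not for events. They make capture differ between leavers and stayers and do not make it uniform.

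**Conclusion.** The point holds as a weakness of the collection method and of one sentence, not as a demonstrated bias. As stated, capture is passive, and the no-risk premise conflicts with the retention section and sits awkwardly with the discontinuation section. If retention differs between arms, recorded counts may partly track retention. The size and direction are unknown: the ratios of 1.00 to about 0.79 rest wholly on assumed dropout of 10–15% versus 20–40% at month 3, detection of 0.8 in therapy and between 0 and 0.8 afterwards, and equal true rates. The lowest value needs no detection at all after leaving, which the provisions for leavers make unlikely. The primary estimate and the sample size are unaffected. I would class it as a cheap improvement.

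**What to change.** 1. Add one adverse event question, worded identically in all arms, to the existing online survey at every scheduled assessment. It should cover the time since the last assessment and go to all randomised patients, whether or not they are still in treatment. Keep spontaneous and observed reports alongside it, and tabulate the source of each event.
2. Report by arm, for all randomised patients, the proportion with reliable deterioration on the ADP-IV and BSI, extending the reliable change already planned. State how many patients contributed data in each arm.
3. Beside it, report the number of treatments ended for worsening or for negative effects.
4. Reconcile the no-direct-risk sentence with the sections on discontinuation and treatment retention.

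The cost is one question at each of the eight assessments from month 1 to month 36, and one table from data already being collected. Patients complete the questionnaires online, so the question need not threaten assessor blinding, and researchers already check responses. The downside is more minor events to log and counts that look less favourable. The question also helps only where the assessment is completed, so it reduces the dependence on retention in therapy but not the dependence on retention in the study.

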### Frequency and plans for auditing trial conduct {23}

No auditing of trial conduct is planned.

### Plans for communicating important protocol amendments to relevant parties (e.g. trial participants, ethical committees) {25}

Important protocol modifications will be communicated with the ethical committee of the VU Amsterdam and if necessary with the therapists and the research participants.

### Dissemination plans {31a}

The trial results will be offered for publication in a peer-reviewed journal. The article will be shared with the therapists and participants of the trial.

Because of the use of privacy sensitive information, the database will not be shared in a public repository.

## Discussion

This article presents the design of I-FORCE, a pragmatic clinical trial comparing the effectiveness of three individual psychotherapies for Cluster-C PDs, short-term psychodynamic supportive psychotherapy (SPSP), affect phobia therapy (APT) and schema therapy (ST). I-FORCE responds to the need to broaden the evidence for the treatment of Cluster-C PDs, a group of patients with high prevalence rates in the general and clinical population.

In the current literature, the number and quality of the conducted studies on Cluster-C PD is fairly low, with small sample sizes [56]. This relatively large RCT will extend the evidence considerably. The broad range of outcome variables will give insight in effectiveness on symptomatic, descriptive and of underlying characteristics of personality pathology. By investigating predictors and moderators, this study moves from general effectiveness to a more tailored insight into differential effects of the treatments and interventions. Repeated assessments of mediators during treatment offer us the option to study the temporal relationships between potential mediators and outcome. With the 2-year follow-up period of this study, we can provide insight in the sustainability of gains of treatment, both at a level of symptoms and personality.

In addition, this study will provide insight into the effectiveness and feasibility of Cluster-C tailored protocols. For the three treatments of this study, well-defined protocols are implemented, addressing the phases of treatment, interventions per phase, number of sessions, intensity of treatment and directions for the therapeutic stance. All protocols have a personalized character, offering a balance between directiveness of the interventions on the one hand and the option for adjustment to the personal needs of the patient on the other hand.

### Strengths

To the best of our knowledge, this is the first study comparing psychodynamic treatments for the Cluster-C population head-to-head to ST, a treatment that has proven its efficacy for this population within one earlier RCT [11]. This RCT will contribute to the body of evidence of the effectiveness of time-limited individual PD treatments.

Another strength is the pragmatic nature of this study. By staying close to the clinical reality and daily practice (e.g. allowing add-on interventions, medication use, no preselection of therapists, no intensive central supervision), we can include a wide range of Cluster-C patients and study the effectiveness in an ecologically valid environment. This implies that the sample is aimed to be representative of the clinical field and results could be generalized to daily mental health practice.

A final strength is that the pragmatic nature of this study is balanced by the deliberate attention for the quality and adherence of the delivered psychotherapies. This is ensured by deployment of qualified therapists, who have attended treatment-specific training and attend peer supervisions frequently throughout the treatment. Adherence and performance will be checked by well-defined treatment adherence checks.

### Limitations

There are several limitations to consider. First, in the design of the study, no inactive control group was added. This means that the influence of the natural course of variation over time cannot be ruled out. We did not include a no-treatment comparison group due to ethical issues involved in withholding treatment for this population seeking specialized PD care.

Second, by including a wide range of patients, Cluster-C PDs and the group of patients with an otherwise specified PD diagnosis, the sample might be more heterogeneous than in studies only including full Cluster-C PDs. However, the inclusion criterion of a predominance and a minimum of five Cluster-C traits and the exclusion of (subthreshold) cluster-A and B PD, ensures that patients with predominantly Cluster-C pathology are included. By adding the otherwise specified PD patients, we expect to better adapt to the clinical practice, where the prevalence of full Cluster-C diagnosis is less common than mixed Cluster-C diagnosis.

Third, we did not adjust the sample size for dropout, which might have a negative impact on the power. However, we expect mixed regression with multiple measurements between pre- and posttreatment will compensate for the potential loss of power due to dropout.

Lastly, there might be some overlap between the delivered psychotherapies. APT and ST both are integrative therapies, using elements of psychodynamic, experiential, cognitive and behavioural therapy. Also, APT and SPSP overlap in some of their interventions and in their focus on developmental needs. It has been suggested that general common factors, and in particular the therapeutic relationship, are the most relevant working mechanisms for psychotherapy. Nevertheless, in practice, we think the approaches are perceptibly different at the level of applied concepts and techniques. In ST, this difference is seen in the focus on the mode model and experiential techniques (e.g. imagery rescripting and chair techniques), in APT in the attention for anxiety regulation, perception of the self and activation of affect. SPSP on the other hand is a more exploratory, supportive treatment, focussing on the levels of discourse used to gain insight. We therefore expect a difference in approach to be perceptible for both therapists and patients. This is checked by the treatment intervention checklist after every session and in the adherence part of the study. In addition, this study investigates if improvement on the therapy-specific working mechanisms differs between the three therapies or if they improve equally over all treatments.

In sum, this study aims to enlarge the body of evidence for the (cost)-effectiveness of psychotherapeutic treatment for Cluster-C PDs. Also, we will get a more in-depth insight into the differential effects of the various ingredients of the Cluster-C treatments. We hope to enhance optimization of the effectiveness of the therapies and enable more personalized treatment decisions for this neglected group of patients.

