### Objectives {7}

The primary aim of this study is to compare the effectiveness and cost-effectiveness of the three individual treatments (SPSP, APT and ST) for Cluster-C PDs. The primary outcome of this superiority study is the severity of Cluster-C PD. We will compare the slopes over time of the three treatments from 0 to 12 months, with assessments of Cluster-C PD severity taking place at baseline, 1, 3, 6 and 9 months. Additionally, we will research differences between the outcomes of the three treatments at 18, 24 and 36 months follow-up. No hypothesis was formulated about the direction of a difference.

The second aim of this study is to explore working mechanisms by focussing on therapy-specific factors in the context of the contribution of common factors across psychotherapies. Selected therapy-specific factors are as follows: therapy-specific interventions; insight for SPSP; change in affect, defence style, perception of the self for APT; change in schema modes for ST. Working alliance is the non-specific factor being investigated.

The third aim is to identify general and specific predictors. Potential moderators will be studied exploratively. Firstly, we hypothesize that patients with relatively more childhood trauma will benefit more from ST than SPSP and APT, because of the use of imaginary rescripting, an evidence-based trauma processing technique [35, 83]. Secondly, we expect that patients with more severe personality pathology (e.g. borderline personality organization (Kernberg, [57]) will profit more from ST or SPSP than APT. This is because these therapies are developed and have proven their effectiveness for a broader range of PDs [60, 88], whereas APT is originally designed for the Cluster-C/neurotic population [25].

The relationship between specific treatment interventions, mediators and outcome will also be explored. Therapists will indicate per session which of the core interventions per treatment they have applied in their sessions. The hypothesis is that certain interventions will be stronger connected to mediators and outcome than others. For example, experiential techniques (imagery rescripting, multiple chair technique) for ST; adequate support for SPSP; facilitation of expression of emotions for APT.

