### Participant timeline {13}

#### Sample size {14}^3^

First, the required sample size was calculated to compare the three types of active treatments. Three pairwise comparisons will be conducted between the active treatment arms (ST vs. APT, ST vs. SPSP; APT vs. SPSP). We want to detect a medium effect size (*f*=0.11) in a pairwise comparison of pre-post change between two active treatment arms, equivalent to *f*(*v*)=.2460 and Cohen’s *d*=.492, with Bonferroni-corrected *p* = 0.0167, a power of 0.80 and within-person correlation coefficient=0.60, for which 88 patients are needed per arm. Because three types of therapies will be compared, 3 × 88 = 264 participants are needed to perform three pairwise comparisons. We chose a medium effect size (f=0.11^4^) since this would also be a clinically meaningful difference, as opposed to a smaller effect size.

The correlation of 0.60 is an educated guess of the correlation between repeated assessments based on the previous RCTs the authors conducted.

The final analysis will be conducted with mixed regression on time series: the change in slope over time between two treatments. Because power analysis for mixed regression are complex and based on complex assumptions about the covariance-structure, a simplified approach was chosen by conducting a power analysis on the pre-post change.

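### The 0.80 power is a complete-data pre-post figure, and the expectation that mixed regression will make up for dropout is asserted, not shown

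*Protocol article*

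**What the plan says.** The section Sample size {14} of the protocol article states the target: "We want to detect a medium effect size (*f*=0.11) in a pairwise comparison of pre-post change between two active treatment arms". On other scales the protocol gives this effect as f(V) = 0.246 and d = 0.492. The Bonferroni-adjusted significance level is 0.0167 for each of the three comparisons. The section's conclusion reads: "a power of 0.80 and within-person correlation coefficient=0.60, for which 88 patients are needed per arm". The total of 264 is three times 88. The same section says that the final analysis will be a mixed regression comparing slopes. It says the pre-post calculation was used as a simplification because mixed-model power needs assumptions about the covariance structure. It calls the 0.60 an educated guess at the correlation between repeated assessments.

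The Limitations section is open about dropout: "Third, we did not adjust the sample size for dropout, which might have a negative impact on the power". It then sets the problem aside: "we expect mixed regression with multiple measurements between pre- and posttreatment will compensate for the potential loss of power due to dropout".

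The section on discontinuing interventions {11b} allows losses ("Patients can leave the study at any moment for any reason if they wish to do so") but forecasts no rate. Treatment retention says that patients who stop treatment are encouraged to complete their scheduled assessments.

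**The concern.** The calculation behind 88 per arm has no dropout term, so its 0.80 holds only if every randomised patient contributes both scores. Enrolment leaves no margin. The only answer offered is that intermediate visits will recover the loss, and how much they recover is set by the covariance structure that the sample-size section declined to assume. The protocol cannot leave that structure open and also rely on what it would imply.

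This affects how a null result is read. The trial makes three comparisons between active therapies, so null findings are plausible. A reader would take each as coming from a comparison with 80% power, which is true only under conditions the protocol does not give.

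**Working it through.** **Inputs from the protocol.** f = 0.11, r = 0.60, alpha = 0.0167 per comparison and 88 per arm (Sample size {14}). The test is taken as two-sided because "No hypothesis was formulated about the direction of a difference" (Objectives {7}).

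**Inputs that are assumed.** Dropout of 20% and 30%, spread evenly over the post-baseline visits, since no rate is stated. Visits at 0, 1, 3, 6, 9 and 12 months: Objectives {7} lists only baseline to 9 months for the 0 to 12 month slope, the Abstract adds 12 months, and the schedule in Table 3 is not visible in the text.

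**Step 1: reproduce the plan's figure.**
- f(V) = f × √(2/(1 − r)) = 0.11 × √(2/0.4) = 0.246, and d = 2 × 0.246 = 0.492 in SDs of the change score.
- The change-score variance is 2(1 − 0.60) = 0.80 in units of a visit's variance, so the difference at 12 months is 0.492 × √0.80 = 0.44 SD.
- λ = N × f(V)² = 176 × 0.0605 = 10.65. The noncentral F with 1 and 174 df at alpha 0.0167 gives power 0.800.

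The stated figure is correct for 88 complete pairs per arm.

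**Step 2: the same test on complete cases only.** With n = 88 × (1 − dropout):

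| Missing | n per arm | Power |
|---|---|---|
| 10% | 79.2 | 0.75 |
| 20% | 70.4 | 0.69 |
| 30% | 61.6 | 0.62 |

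These describe a complete-case pre-post test, which is not the planned analysis.

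**Step 3: the linear-slope mixed model.** The information matrix is the sum over dropout patterns of (patients in the pattern) × X′V⁻¹X, restricted to the visits observed. Power is Φ(0.44/SE − 2.394), where SE is that of the between-arm difference in slope scaled to 12 months. The 0 to 12 month correlation is 0.60 in every pattern.

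Example at 20% dropout:
- Equal correlation: SE = 0.1186, 0.44/0.1186 = 3.71, power = Φ(1.32) = 0.91.
- Pure decay: SE = 0.1441, 0.44/0.1441 = 3.05, power = Φ(0.66) = 0.75.

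| Correlation across visits | 0% dropout | 20% | 30% |
|---|---|---|---|
| Equal, 0.60 between all visits | 0.95 | 0.91 | 0.87 |
| Exponential decay plus residual variance 0.15 (assumed) | 0.85 | 0.79 | 0.75 |
| Pure exponential decay | 0.81 | 0.75 | 0.71 |

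Under this normal approximation, the complete-data pre-post test has power 0.81. Intermediate visits therefore more than cover the loss in the first row, roughly cover it up to 15 to 20% dropout in the second, and do not cover it in the third.

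**Step 4: the same model with a common baseline mean.** This has time and time-by-arm terms and no arm effect at time 0.

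| Correlation across visits | 20% dropout | 30% |
|---|---|---|
| Equal, 0.60 | 0.94 | 0.91 |
| Decay plus residual variance 0.15 | 0.86 | 0.82 |
| Pure decay | 0.84 | 0.80 |

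**Step 5: sensitivity to the visit list.** If only the five visits named in Objectives {7} (0 to 9 months) enter the slope, power under equal correlation is 0.675 before any dropout and 0.583 at 20%. The last visit therefore matters as much as the dropout rate.

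**The case against.** The authors do not hide the problem. They list the missing adjustment as a limitation, call the pre-post basis a simplification, and write only that they expect compensation. That stands: this is a disclosed limitation without a supporting calculation, and the arithmetic behind 88 is right.

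The protocol's single correlation, read literally as 0.60 between all repeated assessments, does deliver compensation: six-visit slope power stays at 0.83 even at 40% dropout. That also stands, so a claim that mixed regression cannot compensate would be wrong. But the 0.60 is described as a guess and was used only for a two-point comparison. Nothing in the document fixes it as equal across all visits.

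Pure exponential decay is a severe case. It has no measurement error and implies a one-month correlation of 0.6^(1/12) = 0.96 for a questionnaire score. The version with residual error is less severe, yet still falls below 0.80 at 20% dropout.

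A reader might also infer from Step 2 that real power is 5 to 18 points below the stated figure. The documents do not support this. The plan is to use all available data in a mixed model, and stopping treatment does not by itself mean a missing score, because those patients are still asked to complete assessments.

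Finally, model parameterisation is usual content for an analysis plan, so its absence here is no fault. The common baseline is offered as an improvement, not as something the protocol wrongly omitted.

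**Conclusion.** The point holds in a limited form. The 0.80 is correct for complete pre and post scores at 88 per arm, and the expectation of compensation for dropout is unsupported rather than refuted. At 20 to 30% dropout, power for the planned type of analysis could lie anywhere from about 0.91 down to about 0.71, depending on the covariance pattern. Against 0.80, that runs from a gain of 11 points to a shortfall of 9.

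These figures rest on assumed dropout rates, even monotone dropout, linear change, a 12-month visit in the slope, a difference of 0.44 SD at 12 months and a normal approximation. The documents give no dropout rate with which to narrow the range.

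**What to change.** 1. In Sample size {14}, label 0.80 as the power of a pre-post comparison with complete data. In Limitations, make the compensation sentence conditional by giving the mixed-model range in Step 3 with its dropout and covariance assumptions. Reconcile the visit list in Objectives {7} with the Abstract, so that it is clear whether the 12-month score enters the slope.

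2. Fit the primary mixed regression with a common baseline mean for the three arms: time and time-by-arm terms, no arm effect at time 0. This is valid because Sequence generation {16a} places the baseline assessment before randomisation. Time 0 must be that score and not the separate start-of-treatment assessment listed in the Abstract. Fix this before any outcome data are examined.

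The cost is a few sentences and one model constraint, with no extra patients or data. The price is a less reassuring power statement. In return, power reaches about 0.80 or more at 30% dropout in all three patterns in Step 4.
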